### ***Secondary objectives***

- To assess and compare the mean or median serum concentrations of interleukin 6 before and after the intervention and between the intervention group with placebo
- To assess and compare the mean or median serum concentrations of ESR before and after the intervention and between the intervention group with placebo
- To assess and compare the mean or median serum concentrations of CRP before and after the intervention and between the intervention group with placebo
- To assess and compare the mean or median of CBC parameters before and after the intervention and between the intervention group with placebo

## **Data analysis**

The data will be analyzed by SPSS software version 25. After examining the normality distribution of variables using Kolmogorov-Smirnov test, quantitative normal variables will be reported as mean $\pm$ standard deviation, quantitative non-normal variables will be reported as median IQR, and qualitative variables as number (percentage). Independent T Test and Mann Whitney test will be used to compare the mean of variables between two groups. Paired T test or Wilcoxon test will be used to analyses within groups means. P-Value <0.05 will be considered as statistically significant. If the patient refuses to continue the study for any reason, statistical methods (Intention-to-treat analysis) will be performed.

1. STEPS, W., *Section 3: guide to physical measurements (Step 2)*, 2008, Geneva.

[figure not shown]

**Figure 1:** Study Process Flow chart

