### **Study Design & randomization:**

The present study will be performed as a Randomized, Placebo-Controlled, Double-Blind, Parallel-Group clinical trial on patients with Covid-19 admitted to Shahid Jalil Hospital in Yasuj (Kohgiluyeh & Boyr Ahmad province, south-west of Iran). The study protocol was approved by the Ethics Committee of the School of Nutrition and Public Health ( ) in Yasuj University of Medical Sciences and is in agreement with the declaration of Helsinki of the world medical association. This study was also registered in the Iranian Center for Clinical Trials ( ). Patients will be randomly divided into two groups of intervention (n=24), and placebo (n=24), by block random sampling method, which randomizes participants into 4 different blocks in each group, based on gender and age . Intervention group receive 500 ml of natural whole pomegranate juice twice a day, after lunch and dinner and control group receive the same amount of placebo with the same color and taste as natural juice. The pomegranate juice and placebo will be administered to patients by two nurses in opposite shifts. Patients will be followed for 14 days and the objectives of the study will be fully explained to the patient and their companions. An informed written consent form will be also obtained.

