### **Clinical, Para clinical and dietary intake assessments:**

A demographic questionnaire containing information about age, sex, habitat, education, occupation etc., will be taken from patients. Medical history and medications/supplements history will also be asked of the patient or his companion.

Height, weight and waist to hip ratio (WHR) will be measured by standard methods [1] as well as the body mass index (division of weight in kilograms to the height in meters squared).

For the purpose of evaluating detailed information about nutrient intake and the food pattern, a 24-hour dietary recall for 3 days (including a weekend day) will be taken by a well-trained interviewer. Dietary intakes will be entered into Nutritionist IV software for further analysis.

10 cc blood samples will be obtained after 12 hour overnight fasting to measure complete blood count (CBC) and inflammatory indices including CRP, ESR & IL-6, at the baseline and by the end of week-2. In the case of patient discharge earlier than scheduled, they will be followed up after discharge and receive pomegranate juice or placebo. The length of hospital stay, disease complications, drug and prescription dosing and mortality rate will be recorded on a daily basis. If the patient refuses to continue the study for any reason, blood sample will be drawn on the same day.

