## **Study objectives:**

### ***Primary objectives***

To assess of the effect of Punica granatum juice on inflammatory biomarkers and CBC in patients with Covid-19

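### The between-arm tests make no adjustment for the baseline marker value, so a valid comparison is less precise than it could be at almost no cost

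*Protocol*

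**What the plan says.** The Data analysis section of the protocol names the test between arms: "Independent T Test and Mann Whitney test will be used to compare the mean of variables between two groups". Within each arm, "Paired T test or Wilcoxon test will be used to analyses within groups means". The choice in each pair follows a Kolmogorov-Smirnov check of normality. The section names no regression, ANCOVA or covariate.

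The section on clinical, para clinical and dietary assessments has blood drawn for "complete blood count (CBC) and inflammatory indices including CRP, ESR & IL-6, at the baseline and by the end of week-2". A baseline value is therefore planned for every marker in the primary objective, which is the "effect of Punica granatum juice on inflammatory biomarkers and CBC in patients with Covid-19".

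The Study Design & randomization section gives "two groups of intervention (n=24), and placebo (n=24), by block random sampling method" and says the method "randomizes participants into 4 different blocks in each group, based on gender and age". Baseline marker level is not among the blocking factors, and the blocking factors do not appear in the analysis. Neither the Secondary objectives nor the Data analysis section says whether the arms are compared on week-2 values or on changes from baseline.

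**The concern.** The trial collects a covariate that may predict the outcome and then leaves it out of the comparison between arms. Baseline enters formally only through the paired tests, and these do not compare the arms. At most it also enters through a change score, which the text does not specify.

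Two things are at stake with 24 patients per arm. One is precision: the residual variance that baseline could explain stays in the standard error. The other is how the result reads once the baseline table is seen. If the arms happen to differ in baseline CRP or IL-6, a week-2 comparison carries part of that difference, while a change-score comparison over-corrects for it.

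**Working it through.** **Plan's own figure.** The sample size of 48 cannot be reproduced, because the protocol gives no effect size, SD, power or dropout rate. The check below therefore takes 24 per arm as given.

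**Inputs from the protocol.** n = 24 per arm (Study Design & randomization). Significance level 0.05 (Data analysis: "P-Value <0.05 will be considered as statistically significant"); the sidedness is not stated, and two-sided is assumed.

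**Assumed inputs, not in the protocol.** The effect is 0.6 SD of the week-2 value. Rho, the correlation between baseline and week 2, ranges from 0.1 to 0.6. The SD is the same at both times.

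**Precision.** In units of the week-2 variance, the residual variance is 1 for week-2 values, 2(1 − rho) for changes and 1 − rho² for ANCOVA. The ratio of change to ANCOVA variance is 2/(1 + rho), which exceeds 1 for any rho below 1. Power comes from the noncentral t distribution with noncentrality 0.6 / (s × sqrt(2/24)), where s is the square root of the variance and sqrt(2/24) = 0.289. For example, week-2 values give 0.6/0.289 = 2.08, and ANCOVA at rho 0.5 gives 0.6/(0.866 × 0.289) = 2.40. The equivalent unadjusted arm size is 24/(1 − rho²).

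| rho | Variance, change | Variance, ANCOVA | Power, week-2 | Power, change | Power, ANCOVA | Equivalent n per arm |
|---|---|---|---|---|---|---|
| 0.1 | 1.80 | 0.99 | 53% | 33% | 53% | 24.2 |
| 0.3 | 1.40 | 0.91 | 53% | 41% | 57% | 26.4 |
| 0.5 | 1.00 | 0.75 | 53% | 53% | 65% | 32.0 |
| 0.6 | 0.80 | 0.64 | 53% | 62% | 72% | 37.5 |

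A simulation of 5,000 trials at rho 0.5 gave 54% (week-2), 53% (change) and 64% (ANCOVA). The formula is thus about one point generous to ANCOVA, because it ignores the small cost of estimating the slope. At rho 0.1 there is no practical gain over week-2 values.

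**Chance imbalance.** The baseline difference between arms has a standard error of 0.289 SD. P(|difference| > 0.3 SD) uses z = 0.3/0.289 = 1.04 and is 30% per marker. P(|difference| > 0.5 SD) uses z = 1.73 and is 8.3%.

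A baseline difference of x SD shifts the week-2 comparison by rho × x and the change comparison by −(1 − rho) × x:
- For x = 0.3, the week-2 shift is 0.03, 0.09, 0.15 and 0.18 SD at rho 0.1, 0.3, 0.5 and 0.6. The change shift is −0.27, −0.21, −0.15 and −0.12 SD.
- For x = 0.5, the week-2 shift is 0.05, 0.15, 0.25 and 0.30 SD. The change shift is −0.45, −0.35, −0.25 and −0.20 SD.

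The type I error conditional on the imbalance uses a normal approximation: mean as above, SE sqrt(1 − rho²) × 0.289, and a critical value of 1.96 times the unadjusted SE. At x = 0.3 it stays at about 4% to 5% under either reading. At x = 0.5 the week-2 test has about 5%, 7%, 10% and 12%, and the change test about 14%, 12%, 10% and 9%.

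**The case against.** The strongest reply is that nothing here is an error. Averaged over randomizations, the planned tests keep their 5% level and the comparison is unbiased, and chance imbalance is already reflected in the standard error. This stands. A reader might infer that the unadjusted result is biased or the test invalid; the documents do not support that.

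A reader might also take the 30% chance of a 0.3 SD imbalance as a 30% chance of a seriously distorted answer. It is not. The shift in the week-2 comparison is only rho times the imbalance, at most 0.18 SD over the range used and below the 0.289 SD standard error. The conditional error at that imbalance is close to nominal. Nor can one say that imbalance is simply left uncorrected: if changes are compared, baseline is used, though imperfectly.

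The gain rests on assumed figures. Baseline is taken during acute illness and follow-up two weeks later, possibly after discharge, so a low rho cannot be excluded. At rho 0.1 to 0.2 the gain over week-2 values is close to nil (power about 53% to 55%). This stands and limits what can be claimed about size.

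It would be too strong to say that severity is unrestricted. Patients are hospitalized, several conditions bar entry, and transfer to intensive care is an exclusion criterion. No figure in the protocol shows how widely the markers will vary.

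The wording that attaches a mean to the Mann-Whitney test might be read as a substantive mistake. The Secondary objectives allow a mean or a median, and non-normal variables are to be summarized by the median, so it is a matter of wording.

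Finally, adjustment is often specified in an SAP, and one may exist that was not available. The protocol does, however, name its between-arm tests, and what it names is unadjusted. That is enough for a recommendation, though not for a charge of omission.

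**Conclusion.** The point holds as an efficiency weakness in a valid analysis. Under either reading of what is compared, ANCOVA on baseline has residual variance no larger than the planned test. Against week-2 values the gain for an assumed 0.6 SD effect runs from nil at rho 0.1, through about 4 points at rho 0.3 and 12 at rho 0.5, to 19 at rho 0.6 (72% against 53%). Against change scores it is larger at low rho (53% against 33% at rho 0.1) and about 10 points at rho 0.6.

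The result is also sensitive to a chance baseline difference, modestly at 0.3 SD and more clearly at 0.5 SD. The direction of the gain is secure for any appreciable rho. Its size is not, because the protocol gives neither rho nor the effect size. The change is worth making because it costs so little, not because the planned test would mislead on average.

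**What to change.** Replace the between-arm sentence in Data analysis with a primary analysis for each marker: ANCOVA of the week-2 value on arm and baseline value, also including gender and age in the form used for blocking. Report the adjusted difference with its 95% CI.

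- For skewed markers that are strictly positive, such as CRP and IL-6, use the log scale for both time points and report the adjusted ratio of geometric means.
- For CBC parameters that can be zero, such as some differential counts, the log is undefined; use the original scale or ranked ANCOVA.
- Keep Mann-Whitney as a sensitivity analysis.

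The cost is the rewritten sentence and a few degrees of freedom. With 48 patients and one term each for arm, baseline, gender and age, the residual degrees of freedom are 48 − 5 = 43, against 46 for the t-test. No new data or patients are needed, and the planned SPSS version can run it.

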## **Material and Methods:**

### **Participants & recruitment:**

Out of the total number of hospitalized patients, 48 patients with definitive diagnosis based on PCR test, who also have other inclusion criteria, are included in the study by availability sampling.

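### Within-arm before-after tests stand unranked beside the between-arm tests at the same 0.05 threshold, so recovery alone could be read as a juice effect

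*Protocol*

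**What the plan says.** Study Design & randomization describes a "Randomized, Placebo-Controlled, Double-Blind, Parallel-Group clinical trial on patients with Covid-19" and divides the patients into "intervention (n=24), and placebo (n=24), by block random sampling method".

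Data analysis plans two kinds of test. Between arms: "Independent T Test and Mann Whitney test will be used to compare the mean of variables between two groups". The next sentence adds the within-arm tests: "Paired T test or Wilcoxon test will be used to analyses within groups means". One criterion then covers both kinds: "P-Value <0.05 will be considered as statistically significant".

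The four secondary objectives (IL-6, ESR, CRP and CBC) share one form. The CRP objective begins "To assess and compare the mean or median serum concentrations of CRP before and after the intervention", and each of the four sets out its comparisons as "before and after the intervention and between the intervention group with placebo". The primary objective speaks only of the effect of juice on inflammatory markers and blood count; it contains no before-after comparison.

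No sentence in the protocol says that the between-arm result decides efficacy, or that the within-arm tests are descriptive.

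**The concern.** The participants are inpatients with COVID-19 whose markers are measured at baseline and two weeks later. Over that time CRP, ESR and IL-6 may fall with natural recovery, with the other drugs the patients receive, and with regression to the mean. A paired test in the juice arm measures all of these together with any juice effect. The placebo arm is there to remove them, and a within-arm test makes no use of it. The protocol also lists transfer to intensive care and death as exclusions; if those patients leave the analysis, the remainder is tilted towards improvement.

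Two misreadings become possible. A significant fall in the juice arm can be reported as an effect of juice. Or significance with juice but not with placebo can be taken as evidence of a difference, although that pattern does not test the difference between arms. As the secondary objectives are worded, either result could be presented as answering part of an objective.

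**Working it through.** **The plan's own figure.** The only design figure is the sample size, "48 patients with definitive diagnosis based on PCR test". It cannot be reproduced, because no power, difference or SD is given with it. For orientation, 24 per arm has 80% power for a between-arm difference of about 0.83 SD. The conclusion here does not depend on this.

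**Inputs from the protocol.** 24 patients per arm (Study Design & randomization); significance level 0.05 (Data analysis).

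**Assumptions.** Tests are two-sided, since sidedness is not stated. All 24 pairs per arm are analysable. Changes are normally distributed. Juice has no effect. Both arms share the same mean change d, in units of the SD of the within-patient change. The protocol gives no value for d, so a range is shown.

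**Step 1: one within-arm test.** The paired t statistic has 23 degrees of freedom and noncentrality d × √24 = 4.899 × d. The chance of significance is p = P(|T| > 2.069). At d = 0.4 the noncentrality is 1.96 and p = 0.467. At d = 1.0 it is 4.90 and p = 0.997.

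**Step 2: the juice-only pattern.** The arms are independent and have the same p, so P(juice significant, placebo not) = p(1 − p). At d = 0.4 this is 0.467 × 0.533 = 0.249. P(exactly one arm significant) is twice that, 0.498.

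**Step 3: the between-arm test.** An independent t test on change was simulated under the same conditions, with 100,000 trials for each d tried.

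| d (SD of change) | Juice-arm test significant | Juice significant, placebo not | Exactly one arm significant | Between-arm test significant (simulated) |
|---|---|---|---|---|
| 0 | 5.0% | 4.8% | 9.5% | 5.1% |
| 0.3 | 29.1% | 20.6% | 41.3% | 5.0% |
| 0.4 | 46.7% | 24.9% | 49.8% | 4.9% |
| 0.5 | 65.0% | 22.7% | 45.5% | 5.0% |
| 0.6 | 80.4% | 15.8% | 31.6% | not run |
| 0.8 | 96.3% | 3.5% | 7.1% | 4.9% |
| 1.0 | 99.7% | 0.3% | 0.6% | 5.0% |

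The simulation also reproduced the within-arm and juice-only columns at the values of d tried (for example 46.7% and 24.9% at d = 0.4).

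**Reading the table.** The two hazards occur at different sizes of recovery. With moderate recovery the juice-only pattern is common. It can never exceed 25%, the maximum of p(1 − p), which is reached at p = 0.5. With large recovery both arms are usually significant, and the risk is that the juice arm is read alone. All rates are per marker.

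**The case against.** The strongest reply is that the valid comparison is already planned. Data analysis specifies independent t and Mann-Whitney tests, and every secondary objective names the comparison with placebo. This stands: a reader might infer that the plan discards its placebo control, and it does not.

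Nor does the protocol contain a rule that claims efficacy from a paired test or from the juice-only pattern. That also stands. The percentages show how often a misleading result would be available to report, not the error rate of a stated decision rule.

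The objectives can be read more kindly, as one comparison of before-after change between arms. But the separate sentence planning within-group tests favours the two-part reading, and the wording does not settle it. A statistical analysis plan, not shown here, might rank the tests. The objectives and the common threshold would still stand in the protocol as they are.

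Three further inferences go too far. That the within-arm tests will be significant needs a recovery size the protocol does not give; at 0.3 SD the chance is 29%. That every objective is affected is wrong, since the primary objective has no before-after part. And there is no basis for assuming that every blood-count parameter shifts during recovery.

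**Conclusion.** The point holds in a limited form: the four secondary objectives and the Data analysis section give within-arm tests the same standing and threshold as the randomised comparison. With no juice effect and equal recovery of 0.3 to 1.0 SD in both arms, the juice-arm test is significant in 29% to 99.7% of trials. It is likely to be significant (80% or more) only if recovery is about 0.6 SD or larger. Significance with juice alone ranges from about 25% near 0.4 SD down to 0.3% at 1.0 SD. The between-arm test of change stays at about 5% throughout, roughly half of which would favour juice.

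These figures rest on the assumed range of recovery and on 24 complete pairs per arm. With fewer pairs each within-arm test is less often significant at a given d, and the juice-only peak, still at most 25%, moves to a larger d. The fault should be corrected but is not fatal, because a valid test is already in the plan.

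**What to change.** 1. State in Data analysis that efficacy conclusions rest only on the randomised between-arm comparison. Say what is compared: change from baseline or, preferably, the week-2 value adjusted for the baseline value that is already collected. The present text speaks only of the mean of variables and does not say which.
2. Reword the four secondary objectives as the between-arm difference in before-after change.
3. Replace the paired t and Wilcoxon P values with a description of within-arm change: mean or median change with a 95% confidence interval.

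The cost is wording changes and fewer P values to report. No extra patients, samples or measurements are needed.
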